### The Follow-Up Phase

Each participant will be followed for a period of 1 year after their enrollment into the study. Both groups will be followed up for 1 year. Each participant will be given a diary to record the falls and other adverse events. They will be followed up monthly over the phone for falls and for occurrence of other adverse events and for improving adherence to the intervention protocols of the study. Every 3 months, they will be followed up physically to assess fall risk, inquire about any fall history, and note any adverse events during that period.

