#### Data Analysis

The data will be entered in Research Electronic Data Capture (REDCap) and will be analyzed using Stata (version 16; StataCorp) software. Data will be stored in a secure server or cloud-based platform. A principal investigator and a co–principal investigator will have access to the REDcap data. The statistician will be given access to the blinded REDcap data. The occurrence of falls and fall risk during the study period will be summarized as frequency and percentages. The number of falls at these time points will be reported using the median (IQR) values. The fall risk score will be reported as mean (SD) or median (IQR) based on the normality of the data. The Mann-Whitney *U* test and Friedman test (chi-square test) will be used to analyze the change in the frequency of falls (%) at each time point between the groups and within the groups, respectively. The chi-square test will be used to analyze the fall risk score category at each time point between the groups. Additionally, repeated measures ANOVA (or Friedman test) and unpaired *t* test (or Mann-Whitney *U* test) will be used to assess the within-group fall risk score at different time points and at each time point within the group, respectively. Poisson regression analysis (both bivariate and multivariate) will be conducted to explore the association between the dependent variable (ie, the number of falls and fall risks assessed using Timed Up and Go and the Performance-Oriented Mobility Assessment) and independent factors (eg, age, gender, education, chronic illness, and intervention category). Adjusted risk ratios with 95% CIs will be reported for the factors included in the multivariate Poisson regression model. The rationality of prescriptions will be summarized using frequencies and percentages. Subgroup analysis will be performed for participants with recurrent fall history and different age categories.

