#### Incremental Cost-Effectiveness Ratio (ICER)

Incremental Cost-Effectiveness Ratio (ICER) will be calculated by dividing the difference in costs between the interventions by the difference in outcomes. The ICER represents the additional cost per unit of outcome achieved by one intervention compared to another.

We will be following the intention-to-treat strategy to analyze the data. Therefore, even participants who discontinue but have at least 1 follow-up will be included in the study to achieve the required sample size, taking into account their age and health status.

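### The number of falls is modelled by Poisson regression and reported as risk ratios, with no stated person-time or overdispersion handling, under an intention-to-treat rule that appears to omit participants with no follow-up

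*Protocol article*

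**What the plan says.** The Data Analysis section of the protocol article plans that "Poisson regression analysis (both bivariate and multivariate) will be conducted to explore the association between the dependent variable" and a list of factors that includes intervention category. The dependent variables are "the number of falls and fall risks assessed using Timed Up and Go and the Performance-Oriented Mobility Assessment", so the model is meant for a recurrent count and for fall-risk measures alike. For all of them, "Adjusted risk ratios with 95% CIs will be reported for the factors included in the multivariate Poisson regression model". The section names no offset, exposure time, robust variance, dispersion check or negative binomial model, and it excludes none of them.

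The between-group test named for falls is the Mann-Whitney U test, which "will be used to analyze the change in the frequency of falls (%) at each time point between the groups and within the groups" (the Friedman test covers the within-group part).

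The analysis set is described at the end of the ICER section. The approach is called intention-to-treat, and it follows from this that "even participants who discontinue but have at least 1 follow-up will be included in the study to achieve the required sample size".

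On observation time, The Follow-Up Phase says that "Each participant will be followed for a period of 1 year after their enrollment into the study". Falls are collected by diary, at three-monthly visits and by telephone: "They will be followed up monthly over the phone for falls and for occurrence of other adverse events".

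**The concern.** Three things do not fit together.

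- **Effect measure.** A log-linear model for the number of falls estimates a ratio of mean counts or, with exposure time, a rate ratio. Risk ratio is the right name only for a binary outcome, such as a fall-risk category.
- **Variance and exposure.** Falls usually cluster in some people, and an ordinary Poisson model sets the variance equal to the mean. Planned follow-up is one year, but a participant with a single follow-up stays in. Unless exposure enters the model, that person's count is treated as if it came from the full period.
- **Analysis set.** A rule that admits discontinuers on condition of one follow-up leaves out, on its plain reading, those with none. That is a modified set. The trial is open-label, so early loss could differ by arm, and the reason given is to reach the sample size, not to protect the comparison.

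The regression is worded as exploratory. Even so, it is the only clinical analysis in the article that promises an effect estimate with a confidence interval, so it is the likely source of the reported size of the effect on falls.

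**Working it through.** **Inputs from the protocol article.** 73% of controls fall; 239 per arm, raised to 263 for 10% dropout; one year of follow-up. **Assumed, because the article gives no figure:** the negative binomial dispersion k, dropout by arm, and time of leaving.

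**The plan's own figure.** Two proportions of 0.73 and 0.73 × 0.80 = 0.584, with 90% power and two-sided 5%, need 221 per arm, or 234 with continuity correction. The stated 239 is within 3% of the latter, and 239 × 1.10 gives 263 per arm (526). This calculation is for a binary outcome and is not affected by the present point.

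**Step 1: overdispersion.** Fix the chance of no fall at 0.27. For negative binomial counts, (1 + kμ)^(−1/k) = 0.27, so μ = (0.27^(−k) − 1)/k. The variance-to-mean ratio is 1 + kμ. Model-based Poisson standard errors are too small by the factor f = √(1 + kμ), and the true coverage of a nominal 95% interval is 2Φ(1.96/f) − 1.

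| k | mean falls μ | 1 + kμ | f | coverage |
|---|---|---|---|---|
| 0 | 1.31 | 1.00 | 1.00 | 95% |
| 0.25 | 1.55 | 1.39 | 1.18 | 90% |
| 0.5 | 1.85 | 1.92 | 1.39 | 84% |
| 1 | 2.70 | 3.70 | 1.92 | 69% |

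A simulation with 263 per arm, no true effect, 10% dropout in both arms and 600 runs per setting gave 95.5% (k = 0), 84.7% (k = 0.5) and 70.3% (k = 1) with model-based standard errors. With robust standard errors it gave 95.7%, 95.5% and 94.8%.

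**Step 2: no offset and unequal dropout.** Let one arm be complete and let 10% of the other leave at time t (in years), with no true effect. The expected ratio of counts is 0.90 + 0.10t.

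- t = 0.25: 0.90 + 0.025 = 0.925
- t = 0.50: 0.90 + 0.050 = 0.950
- t = 0.75: 0.90 + 0.075 = 0.975

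The ratio falls below 1 if the extra leavers are in the intervention arm and rises above 1 if they are in the control arm. In the simulation, with leaving times of 0.25, 0.5 or 0.75 year, dropout of 5% (control) against 15% (intervention) gave about 0.95, and 5% against 25% gave about 0.90. The log person-time offset brought both back to about 1.00. Equal dropout of 10% gave about 1.00 without an offset.

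Robust variance does not cure this bias. At k = 0.5 with 5% against 15% dropout, robust intervals covered 91% without the offset and 96% with it.

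**Step 3: proportion of fallers.** If the excess 10% leave at three months, their chance of a recorded fall is 1 − 0.27^0.25 = 0.279 at k = 0, 1 − (1 + 0.5 × 1.849 × 0.25)^(−2) = 0.340 at k = 0.5, and 1 − 1/(1 + 2.704 × 0.25) = 0.403 at k = 1. The apparent risk ratio is 0.90 + 0.10 × (that chance)/0.73, which is 0.938, 0.947 and 0.955.

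**The case against.** The strongest reply is that the article is silent, not wrong. It names Poisson regression and leaves open the offset, the variance estimator and any fallback model. These are details that an article may leave to the full protocol or the analysis plan, and neither is shown. That stands. A reader might infer that the trial has committed itself to a plain Poisson model in which intervals are certainly too narrow and early leavers count as a full year. The text does not support this. Too-narrow intervals need both overdispersion and model-based standard errors, and the article gives no mean or variance for fall counts. Median and IQR summaries, rank tests and a recurrent-faller subgroup make overdispersion plausible but do not prove it. Bias between arms needs both a missing offset and unequal follow-up, and nothing in the article points to unequal dropout.

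A reader might also carry the coverage figures over to the main comparison of falls. That is not supported either. The regression is worded as exploratory, the named between-group test is Mann-Whitney U, which does not assume Poisson variance, and the sample size rests on two proportions. The loss of coverage applies to the regression only.

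The risk-ratio label is also not wrong throughout. The same model is meant for fall risk from the two mobility tests. If that is analysed as a binary category, Poisson regression does give a risk ratio, and model-based intervals are then too wide, not too narrow.

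Two points do not depend on any unseen document: the risk-ratio label is wrong for the number of falls, and the intention-to-treat label does not match a rule conditional on one follow-up.

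**Conclusion.** The point holds in conditional form and is a should-fix, not a must-fix. As written, a recurrent count observed over unequal periods is modelled with no stated rate or dispersion handling, its effect measure is misnamed, and the intention-to-treat rule appears to drop participants with no follow-up.

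If standard errors are model-based, nominal 95% intervals from the regression cover about 90%, 84% or 69% at k = 0.25, 0.5 or 1, with fallers held at 73%; at k = 0 there is no loss. If there is no offset and dropout differs by 10 points, a true ratio of 1.00 appears as about 0.925 to 0.975 when the extra leavers are in the intervention arm and go between three and nine months. The faller risk ratio would be about 0.94 to 0.96 if they go at three months. Equal dropout leaves the ratio unbiased. The dispersion, the dropout difference and the leaving times are all assumptions. The effect of omitting participants with no follow-up cannot be sized from the article. Physician-level randomization is a separate source of optimism in the intervals and is not counted here.

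**What to change.** - **Model.** Analyse the number of falls by negative binomial regression, or by Poisson regression with robust variance. Use log person-time as offset and baseline fall history, which is already collected, as a covariate.
- **Effect measure.** Report an incidence rate ratio with its 95% interval for falls. Keep risk ratio for fall-risk categories analysed as binary.
- **Analysis set.** Define intention-to-treat as all enrolled participants by allocated arm, with fall time censored at withdrawal. Participants with no follow-up have zero person-time and add nothing to the rate model, so add a sensitivity analysis for them. If they are to be left out, call the set modified intention-to-treat.

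The offset corrects for shorter observation but not for leaving that is related to falling, so numbers and times of withdrawal should be reported by arm.

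The cost is wording, a little more analysis work, and wider intervals where falls are overdispersed. No new data are needed: the diaries and monthly calls already supply person-time.

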#### Incremental Cost-Effectiveness Ratio (ICER)

Incremental Cost-Effectiveness Ratio (ICER) will be calculated by dividing the difference in costs between the interventions by the difference in outcomes. The ICER represents the additional cost per unit of outcome achieved by one intervention compared to another.

We will be following the intention-to-treat strategy to analyze the data. Therefore, even participants who discontinue but have at least 1 follow-up will be included in the study to achieve the required sample size, taking into account their age and health status.

### Study Monitoring

This study will be monitored by the ICMR monitoring team. The investigator will allocate adequate time for such monitoring activities and ensure access to all the above-noted study-related documents and study-related facilities.

#### Data and Safety Monitoring Board

A Data and Safety Monitoring Board will be constituted for this study independent of the study team members. The team will look into the safety of the intervention proposed with an interim analysis report.

#### Interim Analyses

Two interim analyses will be conducted during the study period: the first after the completion of the first follow-up of 200 participants and the second after reaching 400 participants.

### Ethical Considerations

The study will be conducted as per the ICMR National Bioethical Guidelines 2017 [13] and New Drugs and Clinical Trial Rules 2019 [14]. The study received approval from All India Institute of Medical Sciences Bibinagar, Institutional Ethics Committee (AIIMS/BBN/IEC/JUNE/2023/294) on June 16, 2023.

Eligible participants who are willing to participate in the study will be enrolled after obtaining written informed consent.

Confidentiality of participation will be maintained, and personal identity will not be revealed during data collection, analysis, presentations, and publications. Study records will be preserved for 3 years and will be made available only to authorized persons conducting the study and to the funding agencies without revealing participant identities.

Reimbursement of Rs 500 (about US $6) per visit will be provided for participation in the study, as participants will be asked to visit the hospital every 3 months after their enrollment into the study.

For any foreseeable and unforeseeable complication, adequate compensation will be provided depending on the nature of the injury or illness. In addition, trial insurance coverage will be provided for any unforeseeable risks related to the study.

## Results

The study received a grant from the Indian Council of Medical Research–Safe and Rational Use of Medicines (ICMR–SRUM) in October 2023. The study is scheduled to start in June 2024 and conclude by 2026. The study protocol is registered with the Clinical Trial Registry – India (registration number CTRI/2023/12/060516). Data collection and follow-ups are expected to be completed by the third quarter of 2026. The results are expected to be submitted for publication in 2026. Based on the results of this study, modules will be prepared and workshops will be organized for the prescribers on deprescribing interventions. The research findings will be presented at the national/international conference for large-scale public dissemination. The results of this study will be published in indexed peer-reviewed scientific journals. The full protocol, participant-level data set, and statistical code will be made publicly available after the completion of the study.

## Discussion

### Expected Outcomes

Polypharmacy has become a major concern in the geriatric population considering their multimorbid conditions. The number of prescribed drugs tends to increase with age, especially among individuals with multiple comorbidities. Although these drugs are prescribed to treat various conditions, some of them, known as FRIDs, contribute to falls in older people. FRIDS include psychotropic drugs (eg, antipsychotics, antidepressants, benzodiazepines, and sedative-hypnotics), cardiovascular agents (eg, loop diuretics, digoxin, antihypertensives, and antiarrhythmics), and other agents (eg, hypoglycemic drugs, nonsteroidal anti-inflammatory drugs, opioids, anticholinergics, and antihistamines). Reports indicate that falls among the older population are significant causes of morbidity, with FRIDs identified as one of the contributing factors for falls.

Deprescription is defined as systematically removing the drug, reducing the dose, or changing the medication without affecting the patient’s health condition. There are various deprescribing tools available for controlling polypharmacy, but none has been considered as a standard with proven effectiveness, as they are often complicated, tedious, and not user friendly for implementation in the real-world settings.

The ARMOR tool-based deprescribing intervention, which contains 5 steps (Assess, Review, Minimize, Optimize, and Reassess) is very convenient and easy to use by physicians and will help in reducing the falls and fall risk in older people who use FRIDs. It is an effort to approach polypharmacy and inappropriate medications in a systematic and organized fashion. It is a functional and interactive evidence-based tool that considers a patient’s clinical profile and functional status with the primary goal of improving functional status and mobility. This tool also emphasizes quality of life as a key factor for making decisions on changing or discontinuing medications.

A study was conducted to evaluate the implementation of the ARMOR tool to address polypharmacy in a rural nursing care facility. This nonrandomized, single-arm, pre- and postbaseline intervention study design was conducted with 600 residents using the ARMOR tool with an interdisciplinary team as an intervention in 7 centers. The residents were on psychotropic medications, experiencing recent or frequent behavioral disturbances causing distress to themselves or others, and exhibiting significant changes in their medical condition [15]. The results showed a negative trend in pain, falls, and anti-anxiety medication use, along with positive results in terms of reduction in the use of psychotropic medications. The average rate of reduction or improvement in antipsychotic risk with the intervention was 13.9% [15].

In India, there are no randomized controlled studies available on the use of this functional and interactive evidence-based tool. This trial will provide essential insights into the efficacy of the ARMOR tool in reducing falls among the geriatric population taking FRIDs. Additionally, it will provide valuable information on the cost-effectiveness of deprescribing practices, offering significant implications for improving the well-being of older patients and optimizing health care resource allocation. The findings from this study will be pertinent for health care professionals, policy makers, and researchers specializing in geriatric care and fall prevention strategies.

### Conclusions

This randomized controlled trial will provide valuable insights into the potential of the ARMOR tool–based intervention to reduce the risk of falls in older patients and its cost-effectiveness in deprescribing FRIDs. The positive outcomes observed in this study would underscore the importance of medication review and optimization as part of comprehensive fall prevention strategies for the older population. Further, this research will guide the implementation of evidence-based interventions in clinical practice. This study marks the first of its kind to be conducted in India on deprescribing intervention using the ARMOR tool with a randomized control led design.

## Appendix

Multimedia Appendix 1 Peer-reviewer report from ICMR.

## Abbreviations

ARMOR: Assess, Review, Minimize, Optimize, Reassess
FRID: Fall Risk Increasing Drugs
ICMR: Indian Council of Medical Research
REDCap: Research Electronic Data Capture
